#### 4.4.4 Other determinants

The following analysis factors will be defined at subject level using data from the CRF:

- Age groups (years) at the start date of time to event for each endpoint (cf. Section 8.5 for more details). This determinant will be analyzed primarily as a continuous variable. For exploratory purposes, it could also be categorized as followed: 15-17; 18-25.
- Geographical regions: Europe (Belgium, Finland, Germany, Italy, Spain, UK); Asia Pacific (Australia, Philippines, Taiwan, Thailand); Latin America (Brazil, Mexico); North America (Canada, United States).

### 4.5 Handling of missing data and inconsistencies

#### 4.5.1 Missing HPV type at visits

The following rules will be applied for the determination of cervical HPV infections in case HPV type is missing at visits:

| Visit v  | Visit v+1                     | Visit v+2                     | Rule for the determination of cervical HPV infections and clearance                                                                                                          |
|----------|-------------------------------|-------------------------------|------------------------------------------------------------------------------------------------------------------------------------------------------------------------------|
| HPV-X    | Missing HPV type              | HPV-X                         | If the duration between detection date of HPV-x at visit v and detection of HPV-x at visit v+2 is > 150 days → 6-month persistent cervical HPV infection starting at Visit v |
| HPV-X    | Missing HPV type              | No HPV-X                      | Transient cervical HPV infection at Visit v
Clearance* (according to definition 1) of cervical HPV infection at visit v+2                                                 |
| HPV-X    | Missing HPV type (last visit) | -                             | No clearance of HPV-X at visit v+1                                                                                                                                           |
| No HPV-X | HPV-X                         | Missing HPV type (last visit) | Other cervical HPV infection at Visit v+1
No clearance of HPV-X at visit v+2                                                                                              |

\*Clearance (according to definition 2) if there is no HPV of type x at visit v+3.

#### **4.5.2 Other missing data**

Missing and inconsistent data will not be replaced. Thus, subjects from the TVC-1- Control arm cohorts with a missing endpoint measure will not be included in the analyses related to this endpoint. Likewise, subjects with a missing or inconsistent data for a determinant (from behavioral questionnaire or CRF) will not be included in the analyses using this determinant.

In case too many observations have to be excluded due to missing data, data imputation may be performed on a case by case basis for some of the determinants used in the univariate and multivariable analyses.

The choice of the most appropriate imputation method (mean substitution, use of multiple regression etc.) will be done at the time of statistical analysis. It will depend on the percentages and patterns of missing data (missing at random or not). The chosen method will be described and justified in the statistical report.

All analyses performed based on imputed missing data will be considered as sensitivity analyses aimed at confirming or complementing the main results obtained without replacement of missing data.

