#### **4.4.3 Behavioral determinants**

The following behavioral determinants will be defined at subject level using data from the last yearly questionnaire preceding the date of the detection of the reference cervical HPV infection:

- Cigarette Smoking: number of packs per year (one pack will be considered as equivalent to 20 cigarettes):
  - [0;0.5[ pack year (women who never smoked i.e. never tried a cigarette or smoked <1 pack per day for less than 6 months) ;
  - $\geq 0.5$  pack year (women who smoked  $\geq 1$  pack per day for less than 6 months or smoked <1 pack per day for 6 months or more or smoked  $\geq 1$  pack per day for 6 months or more)
- Age at first intercourse (years): Never had sexual intercourse; <15; 15-17; 18-25.
- Number of sexual partners: 0; 1; 2-3;  $\geq 4$ .
- Marital status: Living or lived with a partner; Single.
- At least one previous pregnancy: No; Yes. Parity will also be explored.

The following determinants will be assessed at subject level using data from the CRF of the most recent visit preceding the reference cervical HPV infection:

- Hormones for contraception or another indication: No; Yes.

- Intra-uterine device: No; Yes.
- Sterilized: No; Yes.
- *Chlamydia trachomatis*: No; Yes.

The presence of *Chlamydia trachomatis* at visits following baseline will be derived from the AEs collected in HPV-008 study using the following MedDRA codes for *Chlamydia*: '10008538', '10018185', '10053028', '10061041', '10062780', '10062784', '10064525', '10067186', '10067198'.

In addition, results from *Chlamydia trachomatis* DNA yearly screening will also be used.

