#### **6.1.2 Univariate and multivariable analyses**

Except for the analysis of time to first detected incident cervical HPV infection (or first confirmed persistent 6-month cervical HPV infection), the statistical unit of univariate and multivariable analyses will be the cervical HPV infection related to the analyzed event. In order for the determinants defined at subject level to be used in the analyses, the values of

these determinants will be attributed, for each subject, to all the cervical HPV infections of the subject.

The inclusion of determinants in the models will depend on the meaning of these determinants with regards to the analyzed endpoint. For instance, when analyzing the time to first cervical HPV infection, all determinants linked to cervical HPV infections occurring after the first cervical HPV infection will not be taken into account as determinants in the analysis (cf. Section 8.5 for the lists of determinants used in the analyses).

Changes in the definitions of determinants (i.e. modifications of categorizations) may be performed at the time of the statistical analysis in case:

- one category contains too few subjects as compared to the other modalities of a same factor,
- two highly correlated factors are statistically significant in the multivariable analyses. In such case, the two factors may be combined in one single categorisation or one factor will not be used in the analyses.
- a different expression of a determinant is more meaningful for the interpretation of the results, more particularly for determinants that show an association with the outcome (e.g. the effect of cigarette smoking could be assessed using the cumulative lifetime exposure to smoking rather than using the number of packs per year),
- specific analyses are performed (e.g. analyses restricted to HPV types 16 and/or 18).

Such changes will be documented and justified in the statistical report.

Although described in the frequency distribution tables, the modality “never had sexual intercourse” for some of the behavioral determinants may not be taken into account in the univariate and multivariable analyses.

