#### 6.2.4.5 Statistical methods

The time between persistent cervical HPV infections and lesions will be analyzed using Kaplan-Meier method and Cox regression models.

Kaplan-Meier curves presenting the cumulative probability of lesions following 6-month persistent cervical HPV infections will be displayed and compared between groups for determinants of interest using the Log-rank test (univariate analyses). Cox regression models will be also performed for the univariate analyses in order to obtain unadjusted hazards ratios of the determinants of interest.

In addition, a multivariable Cox regression model will be performed in order to estimate the relative contribution of each determinant adjusting for the simultaneous effects of the other covariates. The model will include: time-independent covariates (e.g., age and region at study entry), time-independent covariates re-assessed at follow-up visits (e.g., behavioral determinants updated over the follow-up period using the yearly behavioral questionnaires) and time-dependent covariates (e.g., concomitant cervical HPV infections, i.e. co-infection). Also, some of the determinants will be distinguished depending on whether they started

before or after the 6-month persistent cervical HPV infections leading to the lesions in order to differentiate their effects in the pathway leading from cervical HPV infection to lesion (cf. Sections 4.4.2 and 4.4.3 for the definition of behavioral and clinical determinants and Section 8.5.1 for the list of determinants that will be taken into account in the analysis).

As the same subject may contribute to more than one observation (e.g., the same women may have several persistent cervical HPV infections of same or different HPV types leading or not to lesions associated with these HPV types), the analysis will be performed using an appropriate approach (counting process, clustering etc.) carried out either by a standard or a stratified Cox model depending on whether i) the recurrent events may be considered as identical or different and ii) the assumption that the estimated proportional hazards are constant over time is fulfilled or not [Andersen et al., 1993; Prentice et al, 1981; Kelly and Lim, 2000; Kleinbaum and Klein, 2005].

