#### **6.2.7.2 Analysis unit**

The statistical unit for this analysis will be the subject.

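### Section 4.5.2 excludes the woman for a missing determinant although the infection is the analysis unit, so read literally her infections with complete data are dropped too

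*SAP*

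**What the plan says.** **Exclusion rule.** Section 4.5.2 of the SAP does not replace missing values, and it states that "subjects with a missing or inconsistent data for a determinant (from behavioral questionnaire or CRF) will not be included in the analyses using this determinant". Imputation is optional, has no stated threshold, and counts only as a sensitivity analysis. The exclusion rule therefore governs the main results.

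**Analysis unit.** Section 6.1.2 says that, except for time to first infection, "the statistical unit of univariate and multivariable analyses will be the cervical HPV infection related to the analyzed event". For time to first infection, section 6.2.7.2 says: "The statistical unit for this analysis will be the subject". Section 6.2.4.5 expects that "the same women may have several persistent cervical HPV infections of same or different HPV types".

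**Where determinant values come from.** Section 4.4.3 defines the questionnaire items "using data from the last yearly questionnaire preceding the date of the detection of the reference cervical HPV infection" and the CRF items "using data from the CRF of the most recent visit preceding the reference cervical HPV infection". Section 6.2.4.5 also speaks of "behavioral determinants updated over the follow-up period using the yearly behavioral questionnaires". The tables in 9.5.1 and 9.5.2 each list nine behavioral or CRF determinants. Eight of the nine are marked as re-assessed; age at the beginning of sexual activity is not.

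**A competing sentence.** Section 6.1.2 adds that the values of "these determinants will be attributed, for each subject, to all the cervical HPV infections of the subject".

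**The concern.** The exclusion is set at one level and the analysis at another. Take a woman with infections first detected at Month 6 and Month 30. Under 4.4.3 her questionnaire values come from two forms: Month 1 for the first infection and Month 24 for the second. Suppose the smoking item on the Month 24 form is blank. The Month 6 infection has a complete smoking value, yet 4.5.2 taken literally removes the woman from every analysis that uses smoking. Her Month 6 infection goes with her, along with any CIN2+ that followed it. The reason is a form completed after that infection began. Nothing in the SAP says that her complete infections are kept.

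Usable infections and their lesions are at stake in the main analyses. The loss gathers in the multivariable models, because one gap in any included determinant is enough. The women most exposed are those with several infections, and previous infection and co-infection are themselves determinants under study.

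**Working it through.** The SAP states no figure on this point, so there is nothing to reproduce. It gives neither a missing rate nor the number of infections per woman. The inputs below are assumptions, shown as ranges.

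**Notation.** *q* is the share of infections lacking a needed value, taken as equal for all women. *j* is the number of infections a woman has. *ρ* is the within-woman correlation of missingness.

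**Step 1: chance that a woman is excluded.** With independent missingness this is 1 − (1 − *q*)^*j*. For *ρ* between 0 and 1 a beta-binomial with mean *q* is used. With *ρ* = 1 it is *q* for every *j*. At *q* = 5%:

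| ρ | j = 1 | j = 2 | j = 3 |
|---|---|---|---|
| 0 | 5.0% | 9.75% | 14.3% |
| 0.3 | 5.0% | 8.3% | 10.8% |
| 0.7 | 5.0% | 6.4% | 7.25% |
| 1 | 5.0% | 5.0% | 5.0% |

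**Step 2: share of infections lost.** Assume 60/25/15% of women have 1/2/3 infections, a mean of 0.60×1 + 0.25×2 + 0.15×3 = 1.55. At *ρ* = 0 the subject rule loses (0.60×0.05 + 0.50×0.0975 + 0.45×0.1426) / 1.55 = 9.2% of infections. An infection-level rule loses *q* = 5.0%. The difference is the share of infections that are complete but dropped:

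| ρ | subject rule | infection rule | complete infections lost |
|---|---|---|---|
| 0 | 9.2% | 5.0% | 4.2 points |
| 0.3 | 7.8% | 5.0% | 2.8 points |
| 0.7 | 6.1% | 5.0% | 1.1 points |
| 1 | 5.0% | 5.0% | 0 |

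**Step 3: sensitivity to the assumptions.** At *q* = 5% and *ρ* = 0, moving the mix from 80/15/5 to 40/30/30 changes the excess from 2.3 to 5.9 points. With the 60/25/15 mix, *q* = 2% gives an excess of 1.8 points (*ρ* = 0) or 0.5 (*ρ* = 0.7), and *q* = 10% gives 7.9 or 2.1.

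**Step 4: why the multivariable model matters most.** If all nine determinants enter and each is missing independently, the share of incomplete infections is 1 − (1 − *m*)^9. For *m* = 0.5%, 1% and 2% this is 4.4%, 8.6% and 16.6%. Small rates per item are enough to reach the values of *q* used above.

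**The case against.** **One value may be shared.** The 6.1.2 sentence that gives the subject's values to all her infections can be read as one value per woman. A gap would then affect all her infections alike and no complete infection would be lost. This is the *ρ* = 1 row, and it stands as a possible reading. It fits poorly with 4.4.3, which calls these determinants subject-level in the same sentence that dates them to the reference infection, and with 4.4.4, which treats age likewise but takes it at each start date. If a shared value is intended, 6.1.2 and 4.4.3 conflict.

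**The word may be loose.** Section 4.5.2 goes on to speak of excluded observations, and 6.2.4.4 words censoring of infections in terms of subjects. Exclusion per record may have been meant. That is plausible, but the rule does not say it.

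**A missing form may not create a missing value.** The last questionnaire before an infection could mean the last one completed. An absent Month 24 form would then be replaced by Month 12. This reduces missingness but does not cover blank or inconsistent items.

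**Stronger readings that the SAP does not support.**

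- A reader might infer that the woman leaves every univariate analysis. The exclusion is limited to analyses using the determinant she lacks.
- A reader might treat a gap on any of the five questionnaires as disqualifying. Section 4.4.3 does not make later forms part of an infection's own value, and a loss so defined would not depend on the number of infections.
- A reader might take higher exclusion of multiply infected women as established. It is a deduction that needs missingness not fully shared and a similar missing rate per infection across women. It vanishes for values fixed per woman and for infections first detected at the same visit.
- A reader might infer biased hazard ratios. Previous infection and co-infection are in the model, and selection related to modelled covariates does not by itself bias adjusted estimates.

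**Conclusion.** The point holds as a mismatch between the exclusion rule and the analysis unit in the lesion and clearance analyses. It does not apply to 6.2.7, where the subject is the unit. Followed as written, with values read per reference infection, 4.5.2 discards complete infections and any lesions linked to them from the main analyses using the determinant concerned.

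The size is modest and cannot be derived from the SAP. Within-woman independence is the upper end of the range shown, and some sharing is likely because infections detected close together draw on the same form. What can be shown is a loss of precision. The change is worth making because it is small and the rule governs the main results, but nothing here shows that the conclusions would differ.

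**What to change.** 1. Reword 4.5.2, for example: *In analyses whose unit is the cervical HPV infection, an infection record (or, for updated determinants, a covariate interval) with a missing or inconsistent value is left out of analyses using that determinant; the woman's other infections are kept. In the analyses of section 6.2.7 the subject is left out.*
2. Reconcile the 6.1.2 sentence on attributing subject-level values with 4.4.3: state for each determinant whether there is one value per woman or one per reference infection. Say also whether the last preceding questionnaire means the last completed or the last scheduled.
3. Report the women, infections and lesions excluded from each model, by number of infections per woman. Section 7 says the primary endpoint analysis was already delivered in August 2011, so the report should also state which exclusion rule was used there.

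The cost is a few sentences and one table, with no new data. Keeping several infections per woman raises no new dependence problem, because 6.2.4.5 already plans robust variances and 6.2.6.4 plans GEE. The result is still a complete-case analysis, so the change removes the avoidable loss and not the missingness itself.

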## **5 CHANGES IN THE CONDUCT OF THE STUDY OR PLANNED ANALYSES**

Not applicable.

## **6 STATISTICAL ANALYSES**

### **6.1 Statistical considerations**

#### **6.1.1 General considerations**

All analyses/summaries will be performed using either SAS version 9.1 or higher. They will be done on all 14 countries of the study pooled together.

Categorical variables will be summarized by the frequency and the percentage of each category. The following statistics will be presented for continuous variables: number of non-missing observations, mean, standard deviation, median and range (minimum and maximum).

Unless specified otherwise, two-sided 95% confidence intervals for percentages will be computed using an exact method based on the binomial distribution (Clopper-Pearson method [Newcombe, 1998]).

#### **6.1.2 Univariate and multivariable analyses**

Except for the analysis of time to first detected incident cervical HPV infection (or first confirmed persistent 6-month cervical HPV infection), the statistical unit of univariate and multivariable analyses will be the cervical HPV infection related to the analyzed event. In order for the determinants defined at subject level to be used in the analyses, the values of

these determinants will be attributed, for each subject, to all the cervical HPV infections of the subject.

The inclusion of determinants in the models will depend on the meaning of these determinants with regards to the analyzed endpoint. For instance, when analyzing the time to first cervical HPV infection, all determinants linked to cervical HPV infections occurring after the first cervical HPV infection will not be taken into account as determinants in the analysis (cf. Section 8.5 for the lists of determinants used in the analyses).

Changes in the definitions of determinants (i.e. modifications of categorizations) may be performed at the time of the statistical analysis in case:

- one category contains too few subjects as compared to the other modalities of a same factor,
- two highly correlated factors are statistically significant in the multivariable analyses. In such case, the two factors may be combined in one single categorisation or one factor will not be used in the analyses.
- a different expression of a determinant is more meaningful for the interpretation of the results, more particularly for determinants that show an association with the outcome (e.g. the effect of cigarette smoking could be assessed using the cumulative lifetime exposure to smoking rather than using the number of packs per year),
- specific analyses are performed (e.g. analyses restricted to HPV types 16 and/or 18).

Such changes will be documented and justified in the statistical report.

Although described in the frequency distribution tables, the modality “never had sexual intercourse” for some of the behavioral determinants may not be taken into account in the univariate and multivariable analyses.

Results of multivariable analyses will be interpreted based on both statistical considerations (e.g., p-values or changes in point estimates of the determinants of interest by a given percentage when they are associated with covariates) and clinical and/or virological aspects (i.e. clinical meaning of the determinants included in the analyses with regards to the analyzed endpoint/outcome).

## **6.2 Statistical methods**

### **6.2.1 Description of study cohorts**

The number and percentage of subjects included in the study cohorts will be tabulated. The flowchart of the study cohorts will be presented as shown in Section 8.1.

### **6.2.2 Subject characteristics**

Subject characteristics (age, country and geographical region) will be described at study entry for the TVC-1-Control arm cohort.

## **6.2.3 Description of endpoints and determinants**

### **6.2.3.1 Endpoints and clinical determinants**

Endpoint and clinical determinants defined in Section 4.3 and in Section 4.4.2 will be summarized over the 48-month follow-up period for the TVC-1-Control arm cohort.

When relevant, endpoint density estimates will be calculated by dividing the number of incident events (i.e. progression to lesion, first cervical HPV infection) by the length of follow-up in person months of subjects at risk.

The description of endpoints will additionally be presented stratified according to clinical or behavioral determinants of interest, such as HPV type.

### **6.2.3.2 Behavioral determinants**

Behavioral determinants defined in Section 4.4.3 will be described at subject level by visit for the TVC-1-Control arm cohort by means of frequency distributions (numbers and percentages of subjects).

## **6.2.4 Analysis of time between persistent cervical HPV infections and lesions**

### **6.2.4.1 Population**

The population for the analysis of time between confirmed persistent cervical HPV infections (6-month definition) and histopathologically-confirmed CIN2+ (or CIN1+, or CIN3+) associated with the same HPV type will be restricted to subjects from the TVC-1-Control arm cohort for whom at least one 6-month persistent cervical HPV infection was detected so that a starting date is available for the computation of the time between persistent infections and lesions.

Subjects with positive or missing HPV DNA at Month 0 for the HPV type associated with the endpoint will be taken into account in the analysis as well as subjects for whom a histopathologically-confirmed CIN2+ (or CIN1+, or CIN3+) associated with a given HPV type is detected prior to the detection of the first 6-month persistent cervical infection of that HPV type (see Sections 6.2.4.3 and 6.2.4.4 for handling this particular case).

The cervical HPV infections of subjects positive for HPV DNA at Month 0 and negative for HPV DNA at Month 6 (for the HPV type associated with the endpoint) will be considered as transient cervical HPV infections. As a matter of fact, such cervical HPV infections may be either transient or persistent but the start date of infections which started before study entry is unknown. Consequently, these infections will not be taken into account in the analyses.

